## Abstract

This study aims to test the feasibility of a randomised clinical trial to evaluate how acupuncture affects atopic dermatitis (AD) symptoms and quality of life and to explore potential biomarkers that may be associated with AD. It is a sham-controlled trial in which 30 eligible patients will be randomly allocated in a 1 : 1 : 1 ratio to one of three groups: verum acupuncture (VA) group 1 (3 times weekly for 4 weeks); VA group 2 (twice weekly for 4 weeks); or sham acupuncture group (SA; twice weekly for 4 weeks). SA will consist of nonpenetrating acupuncture. Outcome measures will include the Visual Analogue Scale for itch, SCORing Atopic Dermatitis, and Eczema Area and Severity Index to evaluate AD symptoms improvement along with the Patient Oriented Eczema Measure and Dermatology Life Quality Index to assess quality of life. Measures will be collected at baseline, once weekly during the treatment period, and after a 4-week follow-up period. Blood collection will be at baseline and 4 and 8 weeks after treatment and compared with healthy controls. Illumina sequencing will be used to profile microRNA expression in each group to explore candidate microRNA biomarkers for specific effects of acupuncture in patients with AD. This trial is registered via US National Institutes of Health Clinical Trials registry (ClinicalTrials.gov) on 15 July 2016, identifier: NCT02844452.

## 1. Background

The prevalence of atopic dermatitis (AD), a chronic relapsing inflammatory skin disease characterized by eczematous and intensely pruritic skin lesions [1, 2], is increasing worldwide [3, 4]. In South Korea, about 13% of children and 3% of adults were reported to be diagnosed with AD in a 2008–2011 survey [5, 6]. Pruritus associated with AD often induces sleeping problems and patients with AD frequently complain of a lowered health-related quality of life; for example, daily activities and/or personal relationships may be restricted [7].

First-line therapy of AD is based on the use of emollients and other systemic and/or topical treatments: topical corticosteroid (TCS) and calcineurin inhibitors are recommended as topical management; antimicrobials, systemic immune-modulators, allergen-specific immunotherapy, and phototherapy are used for systemic management [8–11]. However, other complementary and alternative therapies are commonly used by many patients with AD when conventional treatments yield unsatisfactory relief or produce side effects [12].

In Korea, patients with AD have frequently used Traditional Korean Medicine, such as acupuncture and herbal medicine, for symptom management [13]; however, there have been only a small number of clinical studies of AD treatment with acupuncture and herbal medicine and even fewer studies investigating the therapeutic effect of acupuncture alone [12, 14]. This may explain why a recent systematic review failed to include any randomised clinical trials (RCTs) of acupuncture as treatment of AD [15]. Nevertheless, previous reports have demonstrated that acupuncture exerts an antipruritic effect on pruritogen-induced scratching behaviour in an animal model and on allergen-induced itch in patients with AD [16–19]. Considering its potential antipruritic effect, this highlights the need for rigorously designed and conducted trials in acupuncture field [15].

To overcome some weaknesses of previous studies and to determine whether acupuncture helps AD symptom management, we will conduct a randomised, sham-controlled feasibility trial comparing two different doses of active acupuncture treatment with a sham acupuncture control. We aim to establish the feasibility of recruitment and to determine key features, including optimal acupuncture treatment dose and outcome measures, to inform a large-scale RCT in patients with AD. Additionally, we will explore novel biomarker candidates that may be associated with the antipruritic effect of acupuncture.

## 2. Materials and Methods

### 2.1. Objectives

The aims of this study are (1) to investigate the feasibility of a large-scale randomised clinical trial to test the antipruritic effect of acupuncture treatment compared with a sham acupuncture in patients with AD; (2) to identify the optimal dose and schedule of acupuncture treatment and to identify outcome measures that will reflect symptoms changes; and (3) to discover biomarkers that may be associated with the therapeutic effects of acupuncture.

### 2.2. Hypotheses

Acupuncture treatment will mitigate pruritus and other symptoms of AD and will improve quality of life in patients with AD, compared with sham acupuncture.Three times weekly acupuncture treatment over one month will produce better outcomes than twice weekly acupuncture treatment over one month.Certain biomarker levels might be affected by the therapeutic effect of acupuncture and/or development of AD.

### 2.3. Trial Design

A randomised, sham-controlled feasibility trial will be conducted at the Kyung Hee University Korean Medicine Hospital from June 2016 to April 2017 (Figure 1(a)). In addition to patients with AD, healthy volunteers will be recruited to compare various biomarkers between the groups (Figure 1(b)).

### 2.4. Participants and Recruitment

#### 2.4.1. Patients with AD

*(1) Inclusion Criteria*. Participants who meet all of the following criteria will be included:Age 19 and olderMeeting the Hanifin and Rajka criteria [20], with AD symptoms appearing constantly for at least 3 months prior to study enrolmentScore > 3 points and <8 points on itch Visual Analogue Scale (VAS): 1–10 scaleSCORing Atopic Dermatitis (SCORAD) index score 10–40Not taking prescription drugs for AD for at least 1 month prior to enrolmentAbility to understand the study protocol and to voluntarily agree to participateNot participating in any other research studies for AD for at least 1 month prior to enrolment.

*(2) Exclusion Criteria*. Participants who meet any of the following criteria will be excluded:Severely fluctuating AD symptomsTreatments that are not allowed in this study, for example, oral corticosteroids, which may affect the study outcomesAsthma or bronchitisOther disorders that may affect the outcomes, for example, anxiety or depression.

#### 2.4.2. Healthy Controls

*(1) Inclusion Criteria*. Participants who meet all of the following criteria will be included:Age 19 and olderNo present or past history of allergic diseases such as AD, asthma, or allergic rhinitisAbility to understand the study protocol and to voluntarily agree to participate.

*(2) Exclusion Criteria*. Participants who meet any of the following will be excluded:Pregnant or lactating womenHistory of anaphylaxis, severe hypertension, hypotension, or respiratory diseaseRegular use of antihistamines or steroids during the previous month.

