### 2.10. Outcome Measures

One research nurse who is otherwise not involved in this study will conduct a series of outcome measures: its schedule is depicted in Table 2. There will be no separation between primary and secondary outcomes since it is an exploratory study to evaluate the independent effectiveness of acupuncture to treat AD and to collect outcome data for further study.

Participants with AD will complete all the outcome measures; healthy controls will submit to blood collection and complete the Cold-Heat, Centre for Epidemiologic Studies-Depression Scale (CES-D), and state-trait anger expression inventory (STAXI) questionnaires.

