#### 2.10.10. CES-D

Since it has been reported that depression is strongly associated with AD, evaluating depressive symptoms of the patient is highly recommended [40, 41]. The CES-D is a reliable tool for nonpsychiatric populations and the validated Korean version will be used for this trial [42, 43].

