#### 2.10.11. STAXI

It is widely reported that AD patients have a higher risk of depressive symptoms and a reduced capacity to cope with stress or anger [41, 44]. With a suggested relationship between depression and anger suppression in AD patients [41], assessing the anger trait will be valuable to interpret outcomes in the context of participants' responses.

STAXI is a validated measure for assessing the experience, expression, and control of anger. It has 3 subscales such as trait anger, anger-inside (anger suppression), and anger-outside (anger expression) and consists of a total of 44 questions [45]. The validated Korean STAXI will be applied for this trial [46].

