In this context, we will use a commercial kit (Bio-Plex Pro Human Chemokine 40-plex Panel) for the following 40 chemokines from extracted serum samples: 6Ckine/CCL21, BCA-1/CXCL13, CTACK/CCL27, ENA-78/CXCL5, Eotaxin/CCL11, Eotaxin-2/CCL24, Eotaxin-3/CCL26, Fractalkine/CX3CL1, GCP-2/CXCL6, GM-CSF, Gro-*α*/CXCL1, Gro-*β*/CXCL2, I-309/CCL1, IFN-*γ*, IL-1*β*, IL-2, IL-4, IL-6, IL-8/CXCL8, IL-10, IL-16, IP-10/CXCL10, I-TAC/CXCL11, MCP-1/CCL2, MCP-2/CCL8, MCP-3/CCL7, MCP-4/CCL13, MDC/CCL22, MIF, MIG/CXCL9, MIP-1*α*/CCL3, MIP-1*δ*/CCL15, MIP-3*α*/CCL20, MIP-3*β*/CCL19, MPIF-1/CCL23, SCYB16/CXCL16, SDF-1*α*+*β*/CXCL12, TARC/CCL17, TECK/CCL25, and TNF-*α*.

*(3) Serum Cortisol Measurement*. Cortisol, also called glucocorticoid, is a well-known stress-related hormone associated with the hypothalamic-pituitary-adrenal (HPA) axis and its mechanisms have been elucidated by analysing physiological change in stress response systems on a variety of psychological issues [57–60]. In this study, serum cortisol level will be used to assess HPA function in accordance with the stress response of participants. Total cortisol levels will be measured using ELISA.

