### 2.11. Statistical Methods

#### 2.11.1. Sample Size Calculation

The proposed study is a RCT whose primary aim is to investigate the feasibility to recruit and treat participants with AD with acupuncture and to evaluate acupuncture's antipruritic effects. We will calculate the effect sizes of key outcomes including itch VAS and SCORAD index, to inform power calculations for a further large-scale study. A total of 30 individuals with AD and 20 healthy controls will be recruited during the study period; participants with AD will be randomly assigned in a 1 : 1 : 1 ratio to one of two active acupuncture regimens or sham acupuncture. Healthy controls will not receive any treatment. Considering an estimated 20% dropout rate, we identified the sample size with the advice of a statistician. The statistical significance level will be set at 0.1 considering the applied small size.

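### Anxiety or depression excludes only AD patients and pregnancy or lactation only healthy controls, so part of any baseline AD-versus-control biomarker difference can come from the entry rules

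*Protocol article*

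**What the plan says.** The protocol article prints two separate eligibility lists.

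- **AD patients (section 2.4.1).** Exclusions are severely fluctuating symptoms, treatments not allowed in the study (oral corticosteroids are the example), asthma or bronchitis, and other disorders that may affect the outcomes (anxiety and depression are the examples). An inclusion criterion also requires one month without prescription drugs for AD.
- **Healthy controls (section 2.4.2).** The exclusion list reads "Pregnant or lactating womenHistory of anaphylaxis, severe hypertension, hypotension, or respiratory diseaseRegular use of antihistamines or steroids during the previous month". An inclusion criterion rules out allergic disease. No psychiatric item appears.

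The groups share measurements. Section 2.10 states that "healthy controls will submit to blood collection and complete the Cold-Heat, Centre for Epidemiologic Studies-Depression Scale (CES-D") and the STAXI, and Table 2 marks blood, CES-D and STAXI at baseline for every participant.

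The purpose of the controls is in section 2.3: "healthy volunteers will be recruited to compare various biomarkers between the groups". The Discussion repeats this as an aim. Section 2.10.14 adds that baseline AD-versus-control differences define the pool of candidate miRNAs, within which the better verum regimen is then compared with sham.

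The document links these variables itself. Section 2.10.10 says "depression is strongly associated with AD", section 2.10.11 refers to a "suggested relationship between depression and anger suppression in AD patients", and under section 2.10.13 "serum cortisol level will be used to assess HPA function in accordance with the stress response of participants".

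**The concern.** A case-control contrast isolates the disease only if cases and controls are otherwise selected alike. Here the patient group is cleared of anxiety and depression because these may affect the outcomes, while the control group is not. The conditions removed from one side are ones the document ties to AD and, through anger and the stress response, to STAXI and cortisol. Pregnancy and lactation run the other way: they are screened out of the controls and not, as printed, out of the patients, so they too can produce a serum difference unrelated to AD.

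At stake is the reading of the baseline biomarker comparison, which is a stated aim. Because that comparison fixes the miRNA candidate pool, a difference driven by eligibility could also influence which markers are carried forward to the verum-versus-sham analysis.

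**Working it through.** **1. The two lists side by side**

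| Condition | AD patients (2.4.1) | Healthy controls (2.4.2) |
|---|---|---|
| Anxiety or depression | excluded | not listed |
| Pregnancy or lactation | not listed | excluded |
| Steroids | oral corticosteroids excluded as a disallowed treatment | regular use in previous month excluded |
| Antihistamines | covered if prescribed for AD, or if counted as a disallowed treatment | regular use in previous month excluded |
| Respiratory disease | asthma or bronchitis excluded | history excluded |

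The steroid and respiratory items overlap in part. Allergic disease must differ in a healthy-control design. The clear mismatches are the first two rows.

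**2. Size of the shift: an illustration on assumed inputs**

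The document gives no SD, no prevalence of depression and no AD-control difference. Assume a normal score with SD 1 and an exclusion that removes the top fraction q of AD patients on that score, with controls unscreened. The AD mean then falls by

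shift = φ(z) / (1 − q), where z is the (1 − q) normal quantile.

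- q = 5%: 0.1031 / 0.95 = 0.109
- q = 10%: 0.1755 / 0.90 = 0.195
- q = 20%: 0.2800 / 0.80 = 0.350
- q = 30%: 0.3477 / 0.70 = 0.497

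If the screen correlates only 0.5 with the score, each shift is multiplied by 0.5, giving about 0.05, 0.10, 0.17 and 0.25 SD.

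**3. Effect on the contrast**

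For an assumed true AD-control difference of 0.5 SD, with the exclusion acting directly on the score (cut-off c = 0.5 + z):

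| q | Screen in AD only (0.5 − shift) | Same cut-off in both groups |
|---|---|---|
| 5% | 0.39 | 0.43 |
| 10% | 0.31 | 0.39 |
| 20% | 0.15 | 0.33 |
| 30% | 0.00 | 0.28 |

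The last column adds back the fall in the control mean, φ(c)/Φ(c). With no true difference, the one-sided screen produces a false difference of −0.11 to −0.50 SD, and the same screen in both groups produces none.

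The sign reverses only under a strong screen or a small true difference. For a true 0.3 SD, q = 20% gives 0.30 − 0.35 = −0.05 and q = 30% gives −0.20. At correlation 0.5, even q = 30% leaves 0.30 − 0.25 = +0.05.

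**4. Against what the sample can detect**

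Section 2.11.1 states "A total of 30 individuals with AD and 20 healthy controls will be recruited during the study period". Section 2.11.2 sets a two-sided level of 0.10. At 80% power (assumed for this contrast) the detectable difference is (1.645 + 0.842) × √(1/30 + 1/20) = 2.487 × 0.2887 ≈ 0.72 SD. Shifts of 0.11 to 0.50 SD are not negligible beside that; those of 0.05 to 0.25 SD are more modest.

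**The case against.** The strongest reply is that no CES-D or STAXI comparison with controls is planned. Sections 2.3 and 2.10.14 and the Discussion state a control comparison for blood markers only. The Discussion gives the purpose of CES-D and STAXI as examining anxiolytic and stress-relieving effects of acupuncture. Section 2.10.10 takes the AD-depression link as already reported and does not set out to show it. This stands: that contrast is only inferred from collecting the scales in controls.

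Second, section 2.6 screens on demographics, physical examination, medical history and AD severity. No CES-D cut-off exists, so a sharp cut on the score is the extreme case. A reader might infer that the observed difference will change sign; the documents do not support that, because it depends on an assumed strong screen. Nor does the illustration model cortisol, STAXI or miRNA.

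Third, a reader might infer that the patients' medication rule covers only prescription drugs for AD. It does not: the same section bars treatments that may affect the outcomes, in open-ended terms. Rescue steroid use does not bear on a baseline contrast either.

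Fourth, the article may condense a longer list, so the absence of a pregnancy item for patients may not hold in the full protocol. That limits the point to the lists as printed, which still differ. It also means that no conclusion about how well patients are protected can be drawn from the article.

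None of this removes the one-sided psychiatric criterion or the printed pregnancy/lactation mismatch in a biomarker comparison that is planned.

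**Conclusion.** The point holds in a limited form. As printed, the entry rules select AD patients and controls differently on anxiety/depression and on pregnancy/lactation, so a baseline difference in serum markers, including cortisol, cannot be attributed to AD alone. The same applies to CES-D and STAXI if they are compared.

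The direction on CES-D is toward lower patient scores. The size is not derivable from the document; 0.11 to 0.50 SD, or about half that under a screen correlated 0.5, rests on normality and on 5% to 30% of patients being removed. No size can be given for cortisol, STAXI or miRNA, or for the pregnancy/lactation mismatch.

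A reader might infer that the trial's main comparisons are compromised. They are not: VA1, VA2 and SA are randomised from one patient group under one set of criteria, so their clinical comparisons are untouched. Selection can affect which miRNAs enter the candidate pool, but it does not bias the randomised contrast of a given miRNA.

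**What to change.** 1. Apply the anxiety/depression exclusion to healthy controls as well, by the same method used for patients.
2. Reconcile sections 2.4.1 and 2.4.2 on pregnancy/lactation and on prior medication. The investigators decide the clinical rule; the statistical need is that the two groups follow a common one.
3. If controls are already enrolled, do not attribute AD-control differences in CES-D, STAXI or cortisol to AD alone. Report a sensitivity contrast that drops controls with anxiety or depression identified by the medical-history screen used for patients. Table 2 records medical history for both groups, so the source is already collected. A CES-D threshold should not be used for this, because none was applied to patients.

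The cost is eligibility wording and a few screening questions. The small downside is that a few volunteers become ineligible.

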### 2.5. Recruitment

Advertisements will be posted on notice boards of the hospital and local community centres.

### 2.6. Randomisation and Allocation Concealment

After signing the written consent, participants will undergo a screening test to confirm eligibility. The baseline characteristics including demographics, physical examination, medical history, and severity of AD signs will be used to screen the eligible participants according to the inclusion and exclusion criteria. Individuals with AD will be randomly assigned to one of three groups via block randomisation. Healthy volunteers will not be assigned to a treatment group (Figure 1).

An independent statistician will produce random numbers with the PROC PLAN of SAS 9.2 (SAS Institute Inc., Cary, NC, USA) and transfer them to the Acupuncture and Meridian Science Research Centre (AMSRC) at Kyung Hee University, where each random number will be sealed in a sequentially numbered opaque envelope by a staff member who is otherwise not involved in this study.

At the beginning of the randomisation process, the investigator will call the independent staff in the AMSRC to receive the screening number of the participant. Then the AMSRC staff screening ID and treatment assignment will be documented in the trial master file.

### 2.7. Blinding and Code Breaking

Participants and the outcome assessor will be blinded to the treatment allocation in this trial. Since it is impossible to blind the Korean Medicine Doctors (KMDs) who will give acupuncture treatments, they will be excluded from performing the outcome measurements or analysing data. To ensure participant blinding, an eye patch will be applied to patients during the acupuncture treatment, and they will be unable to see the practice procedures. All the acupuncture treatments, regardless of group assignment, will utilise the Park sham device (AcuPrime Co., Ltd., Exeter, UK), which is applied at the acupoints to block participants from seeing whether or not the acupuncture needles penetrate the skin [21]. The acupuncture needles and device will be maintained in place for 15 min in all treatment groups. If a participant has a serious adverse event and immediate cessation of acupuncture treatment is required, the blinding code will be broken.

### 2.8. Interventions

#### 2.8.1. Acupuncture Treatment

The acupuncture treatments were based on the revised STandards for Reporting Interventions in Clinical Trials of Acupuncture (STRICTA) 2010 recommendations (Table 1) [22]. Both manual acupuncture and intradermal acupuncture treatment will be given. The acupuncture protocols reflect everyday clinical practice in Korean Medicine.

In this study, manual acupuncture treatment is composed of fixed acupuncture treatment and additional acupuncture treatment: partially individualised acupuncture treatment will be performed on the basis of the traditional meridian theory and consensus by experts in acupuncture and AD. The number of applied acupoints per patient per session ranges from 6 to 19: 6 basic points and 10 optional points (3 optional points can be applied bilaterally). All participants with AD will receive acupuncture needling at 6 fixed points: LI11, ST36, and PC6, bilaterally. The optional points include ST43, GB41, LI2, TE3, SI3, TE6, SI2, BL66, LR3, and SP3. The optional acupoints will be added in accordance with individual signs or symptoms, contralaterally to the applied signs or symptoms: ST43 and GB41 for gastric stuffiness or dyspepsia; LI2 and GB41 for tenderness around ST25, diarrhoea, or constipation; TE3 and SI3 for fullness in the chest and hypochondrium; TE3 and TE6 for lower abdominal pain plus tenderness on the chest centre; SI3 and GB41 or SI2 and BL66 for lower abdominal pain, dry skin, or heat in the upper body and cold in the lower body; and LR3 and SP3 for pain in hypogastric region with darkness of the sublingual collateral vessels. A study coordinator will ask participants about symptoms that might require additional acupuncture treatment to reduce the bias. Regardless of group assignment, all manual acupuncture treatment will be performed using Park sham devices to maintain participant blinding. The acupuncture treatment will be done with disposable sterilised stainless needles (40 mm length and 0.25 mm diameter; Dongbang Acupuncture Inc., Bundang, Seongnam, Korea) or Park sham acupuncture needles (AcuPrime Co., Ltd., Exeter, UK) according to the assigned groups. Manipulation technique will be performed to elicit “de qi” sensation. The needle will be inserted up to 5 to 30 mm depending on acupoints and retained for 15 minutes.

After removal of needles, intradermal needles using 1.5 mm press tack needles (Haeng Lim Seo Won Medical Co., Korea) will be given to three acupoints per participant per session: LI11 bilaterally and auricular-Shenmen contralaterally. This is aimed at mitigating AD-related pruritus with LI11 and reducing anxiety level with auricular-Shenmen [16, 23, 24]. Participants will be instructed by study staff to press the applied press tack needles located on LI11 for 3 minutes when they feel severe pruritus.

All acupuncture treatments will be carried out by the same KMD, who was trained for 10 hours to guarantee that he could perform the acupuncture treatments identically according to the predefined protocol.

